**Version Date**

January 27, 2025

**2. Objectives**

Describe in plain language the purpose, specific aims, or objectives and indicate the primary goal(s) of the study (e.g. safety, tolerability, effectiveness, feasibility, pilot study, etc.). State the hypotheses to be tested. State primary and any secondary study endpoints.

The primary research question is whether using a “Hypoglycemia Champion” (HC) to target high risk patients with type 2 diabetes (T2D) is a feasible and effective model of care to reduce hypoglycemia risk in this population. The HC will be a specially trained accountable population manager (APM) who will implement a new clinical guideline intended to reduce risk of hypoglycemia.

The aims of this study are to:

1. Convene meetings with stakeholders (endocrinologists within and outside of KP) to develop an evidence-based, expert consensus clinical guideline, “Hypoglycemia on a Page” (HOAP), for hypoglycemia prevention in patients with T2D at high risk of hypoglycemia; publish HOAP in the KPNC clinical library and disseminate for general use by KPNC diabetes care providers (APMs and PCPs) via regional presentations as the new standard of care;
2. Develop a workflow/clinical pathway for use by a “Hypoglycemia Champion” (HC), a clinical pharmacist/accountable population manager (APM) (“HC APM”) who will proactively outreach and

apply the HOAP guideline in the management of KPNC members identified as having high hypoglycemic risk;

3. Conduct an evaluation of whether usual care augmented by HC APM (augmented usual care) is associated with better diabetes regimen safety among KPNC members at high risk of hypoglycemia compared to patients receiving usual care. The study hypothesis is that at 6 months, eligible members assigned to the HC APM (augmented usual care) will be prescribed safer diabetes regimens compared to usual care (control). Care for all eligible members (usual care and augmented usual care) will include available use of the HOAP guidelines.

### 3. Background

#### a. Scientific Background

Provide the scientific or scholarly background for, rationale for, and significance of the research based on the existing literature and how will it add to existing knowledge. A list of references or bibliography must be included as part of this document or uploaded separately.

Hypoglycemia in patients with type 2 diabetes (T2D) is a significant adverse drug event associated with the hypoglycemia-inducing diabetes medications, insulin and sulfonylureas. Hypoglycemia has been poorly addressed by health plans and all but ignored by national performance metrics such as HEDIS.

Hypoglycemia is common (in a survey of 20,188 diabetes patients from KPNC, 12% reported having  $\geq 1$  severe hypoglycemia events requiring third-party assistance in the previous 12 months), morbid (associated with falls, fall-related fractures, automobile accidents, cardiovascular events, dementia, and even death), and costly (total annual direct medical costs ~\$1.8 billion in 2009 in the US). Hypoglycemia often leads to significant diabetes distress and nonadherence to prescribed diabetes medications. Providers are challenged to address the competing demands of prescribing glucose-lowering medications to meet glycemic targets while avoiding hypoglycemia.

In addition, there are now strategic considerations for reducing hypoglycemia risk. NCQA is proposing a new HEDIS measure assessing emergency department visits for hypoglycemia in older adults with diabetes for measurement year 2023 (MY2023). There is little time to prepare before its proposed implementation in 2023. Unlike most of the existing HEDIS measures, this new measure is focused on patients  $>65$  years of age and is not capped at 75 years of age, which matches the age range where hypoglycemia risk is highest. Hypoglycemia risk can be mitigated, but there exist no well-validated, population management approaches for hypoglycemia prevention. Our proposal intends to address this gap by developing and evaluating a practical population management approach to hypoglycemia prevention.

Severe hypoglycemia is the most common adverse drug effect associated with diabetes medications. However, hypoglycemia in patients with T2D is not adequately recognized, documented, or treated by care providers. Ever since landmark clinical trials (e.g., UKPDS) demonstrated that lowering blood glucose levels reduced the risk of long-term diabetes complications, the medical community has prioritized A1C reduction, often underestimating the risks of diabetes medications, especially hypoglycemia. Each year, approximately 11% of KPNC patients with type 2 diabetes experience severe hypoglycemia (a hypoglycemic episode requiring third-party assistance), with the risk increasing with age and duration of diabetes. (Karter, 2018) In older adults, approximately 13% of emergency department admissions for adverse drug events are due to hypoglycemia (primarily in insulin-treated

patients)(Shehab, 2016), and annual hospital admissions for hypoglycemia now surpass those for hyperglycemia.(Lipska, 2014)

The research question is whether an intervention by a hypoglycemia champion directed towards patients at high risk of hypoglycemia can reduce hypoglycemia events more than usual care (which will include a new treatment algorithm aimed at hypoglycemia risk reduction).

We previously developed a hypoglycemia risk tool which can stratify patients into low, intermediate or high risk for ED visit or hospitalization for hypoglycemia.(Karter, 2017; Karter, 2019) We demonstrated that patients classified as high risk for hypoglycemia were 35 times more likely to have an ED or hospital visit for hypoglycemia in the subsequent 12 months, compared to patients classified as low risk. However, it is important to note that ED or hospital visits for hypoglycemia are just the tip of the iceberg: 95% of patients experiencing severe hypoglycemia are cared for outside of the medical system (i.e., assisted by family or others).(Karter, 2018)

Currently, no well-validated, population management approach for hypoglycemia prevention exists. Front line clinicians need information and guidance on how to minimize hypoglycemia risk while optimizing glycemic control to reduce long-term diabetes complications. Thus, the development and evaluation of interventions to address hypoglycemia risk are needed and are highly relevant to TPMG care delivery, patient safety, and strategic goals of maintaining stellar HEDIS performance metrics.

This work has strategic implications for our organization because a new HEDIS measure proposed for measurement year 2023 will assess emergency department admissions for hypoglycemia in older adults with diabetes. Our proposal will address this gap in organizational clinical care by developing and evaluating a practical, proactive, population management approach to hypoglycemia prevention for members with T2D at high risk of hypoglycemia

**b. Preliminary Data**

Describe any relevant preliminary data.

None

**4. Study Design**

Describe the overall approach of the study (e.g. prospective, interventional, observational, retrospective, etc.). If your study includes more than one group, arm, or subject population, describe that here (for example, a study of both subjects and their caregivers, or a study with both a prospective interventional arm and a retrospective chart review arm).

**Phase 1 (not Human Subjects Research)**

**In Phase 1** of this study (Aims 1 & 2), the investigators will:

- convene meetings with endocrinologists to develop and publish a new hypoglycemia prevention guideline, “Hypoglycemia on a Page” (HOAP) [Aim 1], and
- develop a clinical workflow for a clinical pharmacist/APM Hypoglycemia Champion (“HC APM”) to proactively apply the new guideline [Aim 2]

**Aim 1 – Develop and disseminate “Hypoglycemia on a Page” (HOAP)**

- Develop an evidence-based hypoglycemia prevention algorithm to improve the safety of medication regimens for patients with T2D. As with prior guidelines (e.g., “PHASE on a Page”), the investigators will convene regional and national stakeholders to review evidence, gather clinical insights, integrate feedback, and reach consensus for a single standard clinical care guideline for hypoglycemia prevention in high-risk members across KPNC.
- Disseminate HOAP regionally for use by KPNC diabetes care providers (APMs and PCPs)

**Aim 2 – Develop the workflow protocol for use by the “Hypoglycemia Champion” (HC) APM, a clinical pharmacist who will be trained to apply the HOAP guideline to the proactive management of members at high risk of hypoglycemia. This structural change will be modeled after KP’s highly effective PHASE cardiovascular risk management program.**

**Phase 2**

In **Phase 2** of this study (Aim 3), the investigators will:

- conduct a prospective evaluation of whether proactive intervention by the Hypoglycemia Champion (augmented usual care) is associated with better diabetes regimen safety among KPNC members at high risk of hypoglycemia compared to usual care (control) [Aim 3].

**Aim 3 –Conduct a prospective evaluation of whether proactive intervention by the Hypoglycemia Champion APM (i.e., assignment to augmented usual care group) is associated with better diabetes medication regimen safety among KPNC members at high risk of hypoglycemia compared to usual care (control).**

- Randomly assign eligible patients to receive proactive intervention by the HC APM (augmented usual care group) for comparison to data-only patients receiving usual care. All eligible patients will be managed according to the regionally disseminated HOAP as new standard of care). All medical decisions for all patients (augmented usual care and usual care) are made by each member’s medical care team responsible for his or her care (not by study personnel).
- **Primary Outcome:** Proportion of high-risk patients prescribed safer diabetes regimens (discontinuation at 6 months compared to pre-baseline of sulfonylureas, mealtime [rapid-/short-acting], or mixed insulin) comparing study participants (augmented usual care) to data-only patients (usual care controls). The study hypothesis is that more study participants will be prescribed safer diabetes regimens compared to data-only patients. Baseline pharmacy dispensing data and medication discontinuation orders during follow up will be collected directly from EHR/Clarity tables.
  - i. As researchers, patients will not be contacted directly at any time.
  - ii. All care will be delivered under approved protocols by KPNC clinicians.
  - iii. All evaluation data related to clinical outcomes will be collected directly from the medical record of usual care.
- **Secondary Outcomes:** the investigators will also examine differences between study participants and data-only patients in glucagon prescribing, CGM use, hypoglycemia on the

patient's problem list, HbA1c<8% (HEDIS-defined glycemic control metric), and ED visits or hospitalizations for hypoglycemia based on primary diagnosis. The study hypothesis is that study participants will have more glucagon prescribing, CGM use, and inclusion of hypoglycemia on the problem list, with stable glycemic control (HbA1c<8%), and fewer ED visits or hospitalizations for hypoglycemia. The investigators will also conduct Heterogeneity of Treatment Effect (HTE) analyses by age (<75 vs. ≥ 75 years), enrollment criterion (hypoglycemia prediction algorithm vs ED/hospital hypoglycemia admission), and race/ethnicity.

Assess whether this study involves a clinical trial. Clinical trial means a research study in which one or more human subjects are prospectively assigned to one or more interventions (which may include placebo or other control) to evaluate the effects of the interventions on biomedical or behavioral health-related outcomes.

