**Phase 2**

Data collected from study participants and data-only patients

- Prescribing orders and pharmacy dispensing of medications including
- Durable medical equipment orders and dispensing of continuous glucose monitor devices and supplies
- Relevant lab results (e.g., HbA1c)
- ED visits or hospital admissions for hypoglycemia
- Hypoglycemia on the problem list
- Visit notes

- The duration of an individual subject's participation in the study.

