**Phase 2**

Statistical Design: The primary analysis for Aim 3 will be an intent-to-treat analysis using chi square tests and binomial regression. For the primary outcome, differences in the proportion of patients prescribed safer diabetes regimens (i.e., discontinuation of sulfonylureas, mealtime or mixed insulin) will be assessed at 6 months in the treatment vs. control arms. For the secondary outcomes, differences will be assessed in the proportion of patients who had an ED visit or hospitalization for hypoglycemia within 6 months, were prescribed CGM or prescribed glucagon, and were in glycemic control (HbA1c<8%) between the 2 study arms. The investigators will perform exploratory Heterogeneity of Treatment Effect (HTE) analyses for age, race and enrollment criterion (see above) by testing for statistical interactions with the exposure (treatment arm).

- When applicable, the power analysis.

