**Phase 2**

Power Calculation: In preparation for this proposal, baseline use of hypoglycemia-prone medications (e.g., sulfonylureas, mealtime, or mixed insulin) was evaluated in 3921 KPNC patients identified as “high risk” by the KPNC hypoglycemia risk tool. Among these patients, 75% were on hypoglycemia-prone treatment. Approximately 60% of the intervention arm and 20% of the usual care arm will be prescribed safer diabetes regimens within 6 months compared

to baseline. The minimum number of subjects needed to detect this 40% absolute difference, assuming 90% power and a 10% attrition rate, is 86 patients (43 per arm). With an enrollment size of 200 (100 per arm), this trial is more than adequately powered to detect the hypothesized difference.

- Any procedures that will be used for quality control of collected data.

Data analysts routinely inspect the data for corrupt fields or extreme outliers.

c. Sharing of Results with Subjects

Describe whether results (study results or individual subject results, such as results of standard or research lab tests and genetic tests) will be shared with subjects or their providers and under which circumstances.

N/A

If the study carries a risk of incidental findings, describe your plan for evaluating these and determining whether and how subjects or their providers will be given this information.

N/A

If laboratory results will be shared with subjects or their healthcare providers, verify that the laboratory conducting the test is Clinical Laboratory Improvement Amendments (CLIA) certified.

N/A

Describe how study participants will be updated on research progress via newsletter, summary, etc. Consider incorporating such updates to study participants as part of ongoing retention efforts.

N/A

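### The primary outcome is met by stopping a listed drug class whatever replaces it, so a switch between two hypoglycemia-prone classes can score as a safer regimen

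*Supplement*

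**What the plan says.** All references are to the protocol version dated January 27, 2025.

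- **Section 4, Phase 2, Primary Outcome.** The outcome is the proportion of high-risk patients on safer regimens, meaning "discontinuation at 6 months compared to pre-baseline of sulfonylureas, mealtime [rapid-/short-acting], or mixed insulin". The source is given as follows: "Baseline pharmacy dispensing data and medication discontinuation orders during follow up will be collected directly from EHR/Clarity tables".
- **Section 9b, Statistical Design.** The definition is repeated as "i.e., discontinuation of sulfonylureas, mealtime or mixed insulin", assessed at 6 months and compared between arms by chi-square test and binomial regression, by intention to treat.
- **Section 9b, Power Calculation.** The text describes "baseline use of hypoglycemia-prone medications (e.g., sulfonylureas, mealtime, or mixed insulin" in 3921 high-risk patients and reports: "Among these patients, 75% were on hypoglycemia-prone treatment". It assumes that 60% of the intervention arm and 20% of usual care "will be prescribed safer diabetes regimens within 6 months".
- **Section 9a, data collected for both groups.** The list opens with "Prescribing orders and pharmacy dispensing of medications including".

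**The concern.** The outcome label describes a whole regimen, but the rule beneath it describes a single event, the stopping of a listed class. The two come apart when the stopped class is replaced by another class on the same list. Such a patient meets the rule while remaining on treatment that the plan's own power text calls hypoglycemia-prone.

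The follow-up source named for this outcome is discontinuation orders. By themselves these show neither a new start nor a restart.

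At stake is what the primary comparison measures. The plan intends to conclude that the Hypoglycemia Champion improves regimen safety. If some successes in either arm are class-to-class switches, the success proportions overstate that, and the contrast between arms may be distorted.

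**Working it through.** **1. Which patients meet the rule?** The word *or* can mean (a) any one baseline class stopped, or (b) every listed class used at baseline stopped. A third rule, (c) on none of the three classes at 6 months, is not written anywhere in the protocol.

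| Patient | (a) | (b) | (c), unwritten |
|---|---|---|---|
| Sulfonylurea only; stops it, starts no listed class | success | success | success |
| Sulfonylurea only; stops it, starts mealtime or mixed insulin | success | success | not |
| Sulfonylurea plus mealtime insulin; stops the sulfonylurea only | success | not | not |
| Mealtime insulin only; adds a sulfonylurea, stops nothing | not | not | not |

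The second row is the problem. It is a success under both readings that the text allows. The third row shows that a multi-class user's score depends on a choice the plan does not state.

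**2. The plan's own figure.** The stated minimum is 43 per arm. With p1 = 0.60, p2 = 0.20, mean 0.40, 90% power and two-sided alpha 0.05 (assumed, because the plan gives no alpha):

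n = [1.960·√(2·0.40·0.60) + 1.282·√(0.60·0.40 + 0.20·0.80)]² / 0.40² = 29.39 per arm.

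Rounding up to 30 and dividing by 0.90 for attrition gives 34; with continuity correction it is 39. Dividing 29.39 by 0.75 × 0.90 gives 43.5, close to the stated 43. That the 75% was used this way is my inference. The present point does not depend on it.

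**3. Effect on the contrast.** No switching rate is given, so the following range is assumed. Take 60% and 20% as the net success rates and add 5 or 10 percentage points of misclassified switchers:

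| Where switchers occur | Scored rates | Difference | Risk ratio |
|---|---|---|---|
| Nowhere | 60 / 20 | 40 | 3.00 |
| Both arms, +5 | 65 / 25 | 40 | 2.60 |
| Both arms, +10 | 70 / 30 | 40 | 2.33 |
| Intervention only, +5 | 65 / 20 | 45 | 3.25 |
| Intervention only, +10 | 70 / 20 | 50 | 3.50 |
| Usual care only, +5 | 60 / 25 | 35 | 2.40 |
| Usual care only, +10 | 60 / 30 | 30 | 2.00 |

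Equal switching here means the same share of patients in each arm. It leaves the difference alone and pulls the ratio toward 1. Unequal switching moves the difference up or down.

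**4. Effect on power.** Now suppose instead that 60% and 20% already include switches, which the corrected rule would remove. With 90 per arm (100 less 10% attrition) and two-sided alpha 0.05:

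| Share of successes that are switches | Both arms: rates, power | Intervention only: rates, power |
|---|---|---|
| 10% | 54 / 18, 99.95% | 54 / 20, 99.8% |
| 20% | 48 / 16, 99.75% | 48 / 20, 98.2% |
| 30% | 42 / 14, 99.0% | 42 / 20, 89.8% |
| 50% | 30 / 10, 92.5% | 30 / 20, 34.0% |

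Power stays near 90% or higher except in the extreme one-sided case.

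**The case against.** The best reply is that this is an IRB protocol form with a short analysis section. No separate analysis plan is shown, and Section 9a schedules the development of outcome metrics as its own step. The label is at regimen level, so a net-regimen reading may be what the investigators intend, and the data to apply it are collected in both groups. Some of this stands: code lists, look-back windows and refill gaps can properly be left to a later document. But the definition itself is not left open. Section 9b restates it as an equivalence, and under it the sulfonylurea-to-insulin switch is a success on either reading of *or*.

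A reader might infer more than the text supports:

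- **That stopping any one class is the plan's rule for multi-class users.** No any/all rule is written, so this is a gap and not a stated choice.
- **That all intensification counts as safer.** Adding a drug without stopping a listed class does not meet the rule.
- **That drugs stopped and then restarted will count.** The within-6-months wording appears for this outcome only in the power assumption. Sections 2, 4 and 9b (Statistical Design) all fix the outcome at 6 months.
- **That the error favors the intervention.** The Champion's stated goal is to reduce hypoglycemia risk, and the plan gives no reason to expect excess switching in that arm. Excess switching under usual care would work against the intervention.
- **That a positive result would be uninterpretable.** That goes too far. HbA1c below 8% and hypoglycemia ED visits or admissions are secondary outcomes and give context. The context is limited: Section 3 says that 95% of patients with severe hypoglycemia are cared for outside the medical system.

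**Conclusion.** The concern holds in this form: the stated rule lets a switch between two classes that the plan calls hypoglycemia-prone score as a safer regimen, and it leaves multi-class users without a scoring rule. A positive result would then not be clearly interpretable as a reduction in regimen risk. This rests on the text alone and needs no assumption about frequency.

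The size is unknown. Under the assumed 5 to 10 points, equal switching leaves the 40-point difference unchanged and lowers the ratio from 3.0 to 2.6 or 2.3. Switching in one arm only shifts the difference by 5 to 10 points in either direction. The planned 200 patients are adequate at modest switching rates. The definition should be settled before outcomes are scored, because it concerns the primary endpoint and the remedy is nearly free.

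**What to change.** In Section 4, and identically in Section 9b, define the outcome on the net regimen at 6 months, using prescribing orders and dispensing and not discontinuation orders alone. Success requires all of the following:

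1. A listed class in use at baseline is no longer in use at 6 months.
2. No other listed class has been newly started.
3. No stopped class has been restarted.

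State whether a patient on several listed classes must stop one or all of them. Under a one-class rule, someone who stops a sulfonylurea and stays on mealtime insulin would still succeed, so the choice should be explicit.

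Add a sensitivity analysis of being on none of the three classes at 6 months. Report it among those on at least one at baseline; otherwise the roughly 25% (100% − 75%) not on such treatment could meet it from the outset. Change the power text to refer to status at 6 months.

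The cost is a few sentences and some code on data already planned for both groups. Success rates in each arm would be slightly lower. This governs how outcomes are scored; it says nothing about how any patient should be treated.

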## **15. Risks and Benefits**

### **a. Risks to Subjects**

List the reasonably foreseeable risks, discomforts, hazards, or inconveniences to the subjects related the subjects' participation in the research. Consider physical, psychological, social, legal, and economic risks.

No foreseeable risks, discomforts, hazards, or inconveniences to participants are anticipated.

Describe the probability, magnitude, duration, and reversibility of the risks.

N/A

If applicable, indicate which procedures may have risks to the subjects that are currently unforeseeable.

N/A

If applicable, indicate which procedures may have risks to an embryo or fetus should the subject be or become pregnant.

N/A

If applicable, describe risks to others who are not subjects and risks to Kaiser Permanente

N/A

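### Stable glycemic control (HbA1c<8%) is hypothesised, but the only stated analysis is of between-arm differences, with no margin or confidence-interval rule that could support a conclusion of stability

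*Supplement*

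**What the plan says.** All references are to the protocol version of January 27, 2025.

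- **Section 4, Primary Outcome:** success is discontinuation of sulfonylureas, mealtime insulin or mixed insulin at 6 months.
- **Section 4, Secondary Outcomes:** the hypothesis is more glucagon prescribing, CGM use and problem-list entries, "with stable glycemic control (HbA1c<8%), and fewer ED visits or hospitalizations for hypoglycemia".
- **Section 9b, Statistical Design:** the primary analysis is an "intent-to-treat analysis using chi square tests and binomial regression". No separate method is named for the secondary outcomes. The text reads "For the secondary outcomes, differences will be assessed in the proportion of patients who had an ED visit or hospitalization for hypoglycemia within 6 months", and the same sentence goes on to patients who "were in glycemic control (HbA1c<8%) between the 2 study arms".
- **Section 9b, Power Calculation:** "Approximately 60% of the intervention arm and 20% of the usual care arm will be prescribed safer diabetes regimens within 6 months", and "With an enrollment size of 200 (100 per arm), this trial is more than adequately powered to detect the hypothesized difference". This concerns the primary outcome only.
- **Section 9a:** baseline EMR data are collected for both groups, and the data list includes "Relevant lab results (e.g., HbA1c". The only ED visits and hospital admissions listed are those for hypoglycemia.
- **Section 15a:** "No foreseeable risks, discomforts, hazards, or inconveniences to participants are anticipated".

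The protocol does not define *stable*. It gives no margin, no rule for reading a confidence interval, no expected HbA1c<8% rate and no power for this outcome.

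**The concern.** The intervention succeeds when glucose-lowering drugs are stopped, so loss of glycemic control is the natural counter-risk. The protocol's own background (Section 3a) describes the task as minimising hypoglycemia risk while optimising glycemic control. HbA1c<8% is the only listed outcome able to show a move in the wrong direction, because the event outcomes cover hypoglycemia alone.

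A no-worsening hypothesis needs a stated amount of worsening to be excluded. An assessment of differences without one cannot supply that: failing to find a difference in a trial of this size leaves a sizeable loss compatible with the data. At stake is whether the report can say that regimens became safer with control preserved, or only that no difference was detected.

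**Working it through.** **1. The plan's own figures.** None exists for HbA1c<8%. The only sample-size figure is for the primary outcome: 86 patients (43 per arm) for 60% vs 20%, 90% power and 10% attrition. The pooled two-sided 0.05 formula is

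n = [1.96·√(2·0.4·0.6) + 1.2816·√(0.6·0.4 + 0.2·0.8)]² / 0.4² = 29.4,

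so 30 per arm, or 30/0.9 = 34 after attrition. The stated 43 does not reproduce, but it errs on the large side and has no bearing on HbA1c.

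**2. Inputs.**
- From the plan: 100 per arm, and 10% attrition (90 per arm).
- Assumed: two-sided alpha 0.05, usual-care HbA1c<8% rate of 50-80%, and an illustrative true loss of 10 points.

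**3. Precision.** The 95% CI half-width, taking equal rates p, is 1.96·√(2p(1−p)/n).

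| Usual-care rate | n=100 | n=90 |
|---|---|---|
| 50% | 13.9 points | 14.6 |
| 60% | 13.6 | 14.3 |
| 70% | 12.7 | 13.4 |
| 80% | 11.1 | 11.7 |

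**4. Chance of missing a true 10-point loss** (uncorrected chi-square test, exact enumeration).

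| Usual care vs intervention | n=100 | n=90 |
|---|---|---|
| 50% vs 40% | 69.0% | 73.9% |
| 60% vs 50% | 69.0% | 73.9% |
| 70% vs 60% | 68.4% | 70.6% |
| 80% vs 70% | 62.9% | 66.0% |

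The range is therefore about 63-74%. At an extreme usual-care rate of 90% it falls to about half (49% with 100 per arm, normal approximation).

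**5. Excluding a 10-point loss.** With equal true rates and one-sided 0.025, the power to exclude an assumed 10-point margin is Φ(0.10/SE − 1.96), where SE = √(2p(1−p)/100). It is 29%, 30%, 34% and 42% at rates of 50%, 60%, 70% and 80%. For 80% power at 100 per arm, the margin would have to be (1.96 + 0.8416)·SE, about 16-20 points.

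**6. What continuous HbA1c would add, for the same size of loss.** Assume a normal distribution with usual-care mean 7.6 and SD 1.4 (not in the plan).
- Usual-care rate: Φ((8 − 7.6)/1.4) = 61.2%.
- A 10-point loss gives 51.2%, which needs a mean of 7.96, a shift of about 0.36.
- Standard error with baseline adjustment: 1.4·√(2(1−r²)/100), which is 0.171 at r=0.5 and 0.141 at r=0.7.
- Power Φ(0.36/SE − 1.96): about 55% at r=0.5 and 72% at r=0.7. Unadjusted (SE 0.198) it is about 44%.
- Dichotomised at 8%, the same loss has about 31% power.

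With 90 per arm the standard errors are 0.181 and 0.149, and the adjusted power is about 51% and 68%.

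**The case against.** The strongest case on the other side has five parts.

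- **The plan never says that non-significance will be read as stability.** This is correct. A reader might infer it, but the text says only that differences will be assessed, which does not rule out an estimate with a CI. What remains is that no other criterion for *stable* is given, and a CI without a pre-stated margin cannot settle the question.
- **The plan does not say that the analysis is unadjusted.** Also correct. Binomial regression can carry a baseline covariate, and baseline data are collected. The text is silent, so the point is that adjustment is unstated, not that it is ruled out.
- **Margins and covariates are often left to a separate analysis plan, and none is shown.** This has force for such details. It does not remove the mismatch inside the protocol, which states a no-worsening hypothesis and an assessment of differences for the same outcome.
- **HbA1c<8% was chosen as the HEDIS metric, and mean HbA1c answers a different question.** This stands as a reason to keep the binary measure and add the continuous one beside it.
- **A continuous analysis is no cure.** This stands. For a 0.5-point rise, adjusted power is 83-94%, but under the same assumptions that rise is about a 14-point loss (61% to 47%). For the matching 10-point loss it is only about 55-72%.

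The protocol also leaves medical decisions to each member's care team and has the APM monitor participants for safety (Sections 4 and 9a). That is relevant to care, but it does not provide a between-arm measure of harm.

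**Conclusion.** The point holds in a limited form. The protocol hypothesises stable glycemic control and states no analysis that could establish it. With 100 per arm the CI half-width is about 11-14 points (about 12-15 with 90). A true 10-point loss would be missed about 63-74% of the time with 90-100 per arm.

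These figures rest on a two-sided alpha of 0.05, usual-care rates of 50-80% and a 10-point loss chosen for illustration. None of them is in the documents, so a single percentage would be too precise.

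The documents do not support the stronger reading that the trial will declare stability from a non-significant test. The statement that the trial is more than adequately powered applies to the primary outcome and should not be carried over to HbA1c. This is a secondary outcome, and the primary conclusion is unaffected. It still deserves correction before data lock, because it is the only planned check on the opposite harm.

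**What to change.** 1. Keep HbA1c<8% as the HEDIS metric, and report the between-arm difference adjusted for baseline, with its 95% CI.
2. Add 6-month HbA1c as a continuous outcome, adjusted for baseline HbA1c (ANCOVA), with its 95% CI.
3. Have the clinical team fix and justify a margin before data lock. Use the word *stable* only if the CI excludes that margin; otherwise report the estimate and CI and make no claim of stability.
4. Report by arm the number and proportion with a follow-up HbA1c.
5. Count ED visits and hospitalizations for hyperglycemia in both arms, from the EMR extraction already planned.
6. Reconcile the risk statement in Section 15a with a primary outcome (Section 4) that consists of stopping glucose-lowering drugs.

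The cost is some analysis wording and a few more diagnosis codes, since HbA1c and baseline EMR data are already collected. The downside is that the trial may have to report a weaker conclusion on glycemic control: at this size, even the adjusted continuous analysis has only about 55-72% power for a shift equivalent to a 10-point loss.
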